## Methods/design

### Study setting

The clinical study protocol (CSP) of the MARSYAS II trial was written in accordance with the Recommendations for Interventional Trials (SPIRIT) guidelines and completing the SPIRIT Checklist (see supplemental file). The study was approved by the Austrian health authorities (Austrian Office for Safety in Health) and the local Austrian ethics committees (Linz and Klagenfurt). A thorough feasibility and site qualification was performed prior to the selection of 16 study sites in 4 countries (Austria, Germany, Poland, and the Czech Republic) to ensure the achievement of adequate participant enrollment to reach the calculated target sample size. The clinical research organization (CRO) FGK Clinical Research GmbH (Munich, Germany) and its subsidiaries in the Czech Republic and Poland will coordinate the centers and are responsible for data management and pharmacovigilance. Any protocol modifications will be timely reported to the respective authority.

The primary objective of the MARSYAS II trial is to determine the dose-response relationship of the clinical efficacy of APO-2 multiple dose administration in patients with diabetic foot ulcer at three different dose levels compared to placebo. The secondary objectives are to evaluate the safety and tolerability of APO-2 at three different doses and to generate data on additional clinical endpoints for the conception of a phase III study.

The study design is shown in Fig. 1. The partners of the safety lead-in phase are listed in Table 1.

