### Sample size calculation and power

Sample size calculation for the primary efficacy endpoint is based on the assumptions that after 4 weeks, a wound area reduction of 45%, 50%, and 55% (at a dose of 12.5 U/ml, 25 U/ml, and 50 U/ml, respectively) can be achieved compared to 40% reduction in the placebo group (significance level = 0.05 (two-sided); power = 80%).

Based on estimated wound reductions for each group, a variance of mean of 0.003 was calculated. A standard deviation within groups is estimated 0.156 based on previous studies and expert opinion. The calculated minimal number of patients per group is 23, calculated with Nquery Advisor® (STATCON GmbH, Witzenhausen, Germany) [30].

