### Statistical analysis

For the preceding safety lead-in part of the study, safety data of 12 randomized patients will be summarized after the 4-week treatment period. These data will be evaluated by the DSMB. Unblinding is not planned but is possible if requested by the DSMB. Safety and efficacy results of the safety lead-in phase will be included in the data pool of the entire clinical study for final analysis (i.e., the safety lead-in phase is an integral part of the entire MARSYAS II study).

The main study is designed to evaluate the dose-response relationship for clinical efficacy of topical APO-2 at three dose levels compared to placebo. The minimum effective dose, which is defined as the smallest dose with a discernible, useful effect, will be determined.

The primary endpoint is the assessment of the dose-related, relative reduction in wound area from baseline to week 4 (continuous endpoint). Analysis of the primary and secondary efficacy variables will be based on the full analysis set (i.e., all patients with a measured wound size at baseline, who received at least one dose of IMP and have data available at the end of treatment visit). Details are defined in a statistical analysis plan. If data are normally distributed, one-way analysis of variance (ANOVA) will be calculated, including a Dunnett multiple comparison post hoc test, to test each of the active doses against placebo. If Gaussian distribution is not given, a non-parametric Kruskal-Wallis test with Dunns post hoc tests will be performed. If at least one of the doses is statistically significant, then the dose-response relationship is established. In addition, a dose-response model will be developed and tested. Three candidate models (linear, quadratic, and logistic) will be fitted to the data and the Akaike Information Criterion will be used to select the best model. Confidence bands for the estimated dose-response curve will be presented. Binary endpoints will be analyzed by displaying the number and percentage of patients in each dose group. Differences among dose groups will be tested using Fisher’s exact test. For the evaluation of the continuous endpoints, data will be analyzed as absolute values and changes from baseline will be represented by basic statistics (mean, standard deviation, minimum, first quartile, median, third quartile, maximum). A detailed description of the reports and tests is specified in a statistical analysis plan.

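### One dose differing from placebo, in either direction, is taken to establish the dose-response relationship; it shows only that this dose differs from placebo

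*Protocol article*

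**What the plan says.** Under Study setting: "The primary objective of the MARSYAS II trial is to determine the dose-response relationship of the clinical efficacy of APO-2", at three dose levels against placebo. Under Statistical analysis, the primary endpoint (relative wound area reduction to week 4) is tested by one-way ANOVA with Dunnett comparisons of each dose with placebo or, if the data are not normal, by Kruskal-Wallis with Dunn comparisons. The decision rule follows: "If at least one of the doses is statistically significant, then the dose-response relationship is established".

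Linear, quadratic and logistic models are then fitted in addition, with selection by the Akaike criterion and confidence bands. The section also says that a minimum effective dose will be determined.

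Sidedness appears only under Sample size calculation and power: "significance level = 0.05 (two-sided); power = 80"%. The planning means are "a wound area reduction of 45%, 50%, and 55% (at a dose of 12.5 U/ml, 25 U/ml, and 50 U/ml, respectively"), "compared to 40% reduction in the placebo group".

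**The concern.** A Dunnett or Dunn comparison tests one dose against placebo. Rejecting it says nothing about whether the response rises with dose, and under a two-sided test it does not even say that the dose helped. Yet the protocol treats one rejection as success on the primary objective. The planned alternative is an increasing profile (40, 45, 50, 55%), and the objective concerns clinical efficacy. A rule that is also met by a decreasing profile among the active doses, by an isolated effect at the lowest dose, or by uniform harm does not separate the planned finding from these others. The trial could report its primary objective as met on data that do not support that statement.

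**Working it through.** **Inputs.** Means 0.40, 0.45, 0.50, 0.55, SD 0.156, two-sided 0.05, 23 per group (Sample size calculation and power). Total of 132 (Abstract, Trial status) and at least 12 lead-in patients (Standard study procedures). The article gives no main-study number per arm. I take (132 − 12)/4 = 30 as an inference and show 23 and 33 (= 132/4) as the range. Two-sidedness of the Dunnett tests is carried over from the sample size section. Dropout is set to zero because the article gives no rate.

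**Step 1. Reproduce the planned 23.** The variance of the means is (0.075² + 0.025² + 0.025² + 0.075²)/4 = 0.0125/4 = 0.003125; the article rounds it: "a variance of mean of 0.003 was calculated". For the ANOVA F test, λ = 4n × 0.003125/0.156². At n = 23, λ = 0.2875/0.024336 = 11.81 and power is 81.5%. At n = 22 it is 79.5%. So 23 is reproduced as an omnibus ANOVA figure. (The rounded 0.003 gives 79.8% at 23 and would need 24.)

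**Step 2. How often the stated rule is met.** Each dose has t = (mean of dose − mean of placebo)/(s√(2/n)), and the rule is met if any |t| exceeds the two-sided Dunnett critical value (2.39 at 23 per arm, 2.38 at 30 and 33). At n = 30 the standard error is 0.156 × √(2/30) = 0.0403, so differences of 5, 10 and 15 points have noncentrality 1.24, 2.48 and 3.72. Simulated share of trials declaring a dose-response:

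| True means (placebo; low, medium, high) | 23/arm | 30/arm | 33/arm |
|---|---|---|---|
| Reversed: 0.40; 0.55, 0.50, 0.45 | 83.6% | 92.6% | 94.8% |
| Low dose only: 0.40; 0.55, 0.40, 0.40 | 81.8% | 91.7% | 94.1% |
| All worse: 0.40; 0.30, 0.30, 0.30 | 66.4% | 78.5% | 82.2% |
| No effect: all equal | 5.0% | 5.0% | 5.0% |

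In the third row essentially every rejection is in the harmful direction. If the lead-in patients are pooled (33, 30, 39 and 30 per arm), the first three rows become 94.2%, 93.0% and 82.2%.

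**Step 3. A test that uses dose order.** Take the linear contrast c = (−3, −1, 1, 3), with noncentrality Σcμ/(0.156 × √(20/n)). At n = 30 the denominator is 0.1274.

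- Planned means: Σcμ = 0.50, noncentrality 3.93.
- Reversed: 0.10, giving 0.79; the two-sided test rejects in about 12%.
- Low only: −0.15, giving −1.18; rejection in favour of APO-2 is below 1%.
- All worse: −0.30, giving −2.36; rejection in favour of APO-2 is below 1%.

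**Step 4. Power under the planned means, two-sided 0.05.**

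| Per arm | Any-dose Dunnett | Linear contrast | Gain |
|---|---|---|---|
| 23 | 83.6% | 92.5% | 8.9 points |
| 30 | 92.6% | 97.3% | 4.7 points |
| 33 | 94.8% | 98.3% | 3.5 points |

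**Step 5. Other shapes, 23 per arm.** For a 15-point plateau (0.55 at every dose) the linear contrast has 86.4% against 95.0% for Dunnett. For an inverted U (0.40; 0.45, 0.55, 0.45) it has 39.7% against 81.1%.

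**The case against.** The strongest defence is that placebo is dose zero, so any departure from a flat curve is a dose-response in the broad sense, and error against no difference is held at 5%. That stands for equal benefit at all doses: a reader might call a +10 plateau a false dose-response claim, but it is a legitimate plateau, and a plateau contrast would also detect it. The defence does not cover uniform harm, because the objective concerns efficacy. Nor does it justify reading an order among the doses into a reversed or low-dose-only profile.

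Second, the same section models the curve and seeks a minimum effective dose, so a harmful or reversed profile would be visible, and the trial is labelled exploratory. This lowers the severity. But the modelling comes in addition and does not enter the rule, and the Akaike criterion as described ranks shapes without testing against a flat curve.

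Third, an order-free test is defensible when the shape is unknown, as Step 5 shows. This stands against relying on one linear contrast, but not against correcting what a Dunnett result is said to prove.

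Three stronger readings are not supported:

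- A reader might say that about 11 points of power are wasted. That is the omnibus F test (81.5%) against a linear contrast (92.5%) at 23 per arm, whereas the stated rule is any-dose Dunnett. The gap to that rule is smaller and holds for near-linear means only.
- A reader might infer that Dunnett requires a significant F test first. The text does not clearly say so.
- A reader might fault the unordered Fisher test for the responder endpoint ("Differences among dose groups will be tested using" it). For a secondary endpoint that is a preference, not an error.

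**Conclusion.** The point holds as a flaw in the decision rule. As written, it establishes that some dose differs from placebo, and the protocol calls this a dose-response relationship. At 30 per arm the rule is met in about 93%, 92% and 78% of trials under the reversed, low-dose-only and all-worse profiles (84%, 82% and 66% at 23 per arm). Family-wise error with no effect at all is sound at 5%, and the sample size matches the planned ANOVA, so the trial is not underpowered on its own assumptions.

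The power gain from an ordered test is secondary: about 9 points at 23 per arm, 5 at 30 and 3.5 at 33, and only if the profile is close to the planned straight line. The figures rest on normal data, SD 0.156, two-sided testing, no dropout and the inferred arm size. The Kruskal-Wallis and Dunn route was not computed, but the same reasoning applies. This should be fixed; the exploratory status and the planned modelling keep it from being fatal.

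**What to change.** Before unblinding, replace the decision sentence in the protocol and carry the change into the statistical analysis plan:

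1. Word a significant Dunnett or Dunn result as dose X differs from placebo, and count it as efficacy only in the direction of greater wound reduction.
2. Base the dose-response claim on a prespecified trend or multiple-contrast test in that direction, with contrasts built from the planned candidate shapes plus a plateau contrast.
3. Keep Dunnett for the per-dose comparisons.
4. State what each contrast supports. A plateau contrast compares placebo with the average of the doses. The reversed profile averages (0.55 + 0.50 + 0.45)/3 = 0.50, as an equal +10 plateau does, so this contrast can be significant there too. It supports an overall drug effect, not a rise with dose; the shape should be read from the contrasts and fitted models together.

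The cost is text only, with no new patients or data. The downside is that a single linear contrast loses power for plateau or non-monotone shapes (Step 5); the plateau contrast and the retained Dunnett tests mitigate this.

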### Study endpoints

The primary endpoint is wound area reduction after 4 weeks of treatment with APO-2, i.e., wound area at visit 14 (end of treatment visit) compared to visit 2 (randomization). Secondary endpoints are > 50% reduction in wound area after 4 weeks (binary outcome); wound size at baseline and 1, 2, 3, 4, 6, 8, and 12 weeks after the first application of IMP; proportion of patients with complete wound closure during the 12-week follow-up period (100% re-epithelialization of the wound surface with the absence of drainage); time to complete wound closure; recurrence rate of the ulcer during the 12-week follow-up period; clinical assessment of peripheral neuropathy at baseline, 4, and 12 weeks after the first application of IMP; number of patients with local adverse events or serious adverse events (SAEs) with causal relationship to study medication; evaluation of wound pain by visual analogue scale (VAS) at baseline, at every treatment visit, and 4, 6, 8, and 12 weeks after the first application of IMP; and evaluation of quality of life using Wound QoL questionnaire at baseline, 4, and 12 weeks after the first application of IMP.

Patients who discontinue the trial prematurely after having received at least one dose of IMP will be regarded as “early termination,” and the circumstances and reasons of their discontinuation must be documented in the eCRF. All effort should be done to follow-up with the patient visit schedule as per protocol, but at least a complete end-of-treatment examination should be performed.

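### Binary efficacy endpoints are tested only with Fisher's exact test, which ignores dose order; under the planned pattern this costs about 11 to 13 points of power on the >50% responder endpoint

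*Protocol article*

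**What the plan says.** The Study setting section states that the primary objective "is to determine the dose-response relationship of the clinical efficacy of APO-2" at three dose levels against placebo. The Statistical analysis section repeats it: "The main study is designed to evaluate the dose-response relationship for clinical efficacy of topical APO-2 at three dose levels compared to placebo".

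The Study endpoints section opens its secondary list with "> 50% reduction in wound area after 4 weeks (binary outcome") and also includes complete wound closure and ulcer recurrence.

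For binary endpoints, the Statistical analysis section gives counts and percentages per dose group and then one test: "Differences among dose groups will be tested using" Fisher's exact test. The linear, quadratic and logistic dose-response models are described just before this, with the continuous primary endpoint. The same section leaves further detail of reports and tests to a statistical analysis plan that is not shown.

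The Sample size section assumes "a wound area reduction of 45%, 50%, and 55% (at a dose of 12.5 U/ml, 25 U/ml, and 50 U/ml, respectively"), "compared to 40% reduction in the placebo group (significance level = 0.05 (two-sided); power = 80"%). The assumed effect therefore increases at every dose step.

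**The concern.** Placebo, 12.5, 25 and 50 U/ml are ordered groups. Fisher's exact test on a 2x4 table gives the same p-value however the four dose labels are permuted. It asks whether the groups differ in any way, while the trial asks whether response rises with dose. If the truth resembles the planned pattern, a test that uses the order has more power with the same patients. A significant Fisher result would not by itself show that response increases with dose.

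This matters because the Discussion treats >50% reduction as the clinically relevant threshold and names complete closure as the necessary primary endpoint for phase III. Both are binary secondary endpoints meant to guide the next trial.

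**Working it through.** **Inputs.** Mean reductions of 40, 45, 50 and 55%, SD 0.156, two-sided 5% level and 23 per group come from the Sample size section. The total of 132 is in the Abstract. The lead-in of 9 medium-dose and 3 placebo patients is in Standard study procedures, and its pooling into the final analysis is in Statistical analysis. Equal allocation in the main phase is in Study setting.

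**Step 1: the plan's own sample size.** The article says "a variance of mean of 0.003 was calculated". The four means average 0.475, so V = (0.075² + 0.025² + 0.025² + 0.075²)/4 = 0.003125. For a one-way ANOVA with four groups of n, the noncentrality is 4nV/SD². At n = 23 this is 4 × 23 × 0.003125/0.156² = 11.81, and power is 81.5%. At n = 22 power is 79.5%. So 23 per group reproduces. With the rounded V of 0.003, power at 23 is 79.8%.

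**Step 2: responder rates.** The article states none. Assuming normal reductions, the rate is 1 − Φ((0.50 − mean)/0.156):
- placebo: 1 − Φ(0.641) = 26.1%
- low: 1 − Φ(0.321) = 37.4%
- medium: 1 − Φ(0) = 50.0%
- high: 1 − Φ(−0.321) = 62.6%

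**Step 3: group sizes.** If the 12 lead-in patients count towards the 132, the main phase has (132 − 12)/4 = 30 per arm. Pooling the lead-in gives placebo 30 + 3 = 33, low 30, medium 30 + 9 = 39, high 30.

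**Step 4: power by exact enumeration of all 2x4 tables**, two-sided 5% level. Fisher's test is the Freeman-Halton extension. The trend test is the exact conditional Cochran-Armitage test.

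| Group sizes | Fisher | Trend, scores 0,1,2,3 | Difference | Trend, scores 0,12.5,25,50 | Difference |
|---|---|---|---|---|---|
| Pooled 33/30/39/30 | 75.6% | 87.2% | 11.6 | 86.6% | 11.0 |
| 30 per arm | 72.5% | 85.1% | 12.6 | 84.7% | 12.2 |
| 23 per arm | 58.7% | 74.0% | 15.3 | 73.9% | 15.2 |

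With a common rate of 40% in all arms, both tests reject in at most 5.0% of trials. The difference is not bought with type I error.

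**Step 5: other rising rates.** Four other assumed sets (25 to 55%, 30 to 60%, 30/35/45/55% and 30/40/50/65%), at 30 to 33 per arm or pooled, give differences of 12.0 to 15.5 points with the exact trend test.

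**Step 6: other shapes**, 30 per arm, trend power minus Fisher power in points:

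| Shape (placebo/low/medium/high) | Equal scores | Dose scores |
|---|---|---|
| Full plateau from low dose, 26/63/63/63% | −10.0 | −19.8 |
| High dose only, 26/26/26/63% | −7.3 | +2.2 |
| Early plateau, 26/50/63/63% | +3.6 | −2.8 |
| Rise then fall, 26/50/63/50% | −18.1 | −32.5 |

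The advantage therefore depends on the shape of the response and on the scores.

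**The case against.** The strongest reply is that nothing here is an error. Fisher's test holds its level, the main phase is called exploratory, and the sample size is claimed for the primary endpoint only. Dose-response is modelled on the continuous week-4 reduction, from which the >50% endpoint is dichotomised. An omnibus test is also defensible when the shape is unknown, and the quadratic candidate model shows that a downturn is considered possible. All of this stands, and it limits the point to efficiency and fit to the question.

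The sentence might also mean pairwise tests. High dose versus placebo then has 75.7% power at 30 per arm, or 57.5% at 0.05/3. Both are below the 85.1% of the trend test, and the article names neither the pairs nor a multiplicity rule.

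A reader might infer three stronger things that the documents do not support:
- **Fisher's test should be replaced or made merely descriptive.** Step 6 shows it can be the stronger test even under monotone shapes such as a plateau. A descriptive test would not protect against those shapes.
- **Every binary endpoint loses this much power.** The calculation covers >50% reduction only. The article gives no basis for closure or recurrence rates.
- **The plan provides no effect measure.** Percentages per group will be shown, from which differences can be read. Confidence intervals may be in the analysis plan that is not shown.

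**Conclusion.** The point holds as a mismatch between test and question on secondary endpoints. The one test named for binary endpoints cannot use dose order, in a trial designed around dose order. Under the plan's own effect pattern, the cost on the >50% responder endpoint is about 11 to 13 points of power at the expected numbers, and about 15 at the minimum of 23 per arm.

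This rests on normally distributed reductions, the planned means and SD, all enrolled patients being evaluable, the 12 lead-in patients counting within the 132, and a true response that rises as planned. Under a plateau from the low dose or a downturn the comparison reverses. It is not a validity fault, and it does not affect the primary analysis.

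**What to change.** In the Statistical analysis section, for >50% reduction and complete closure:
- add a prespecified exact Cochran-Armitage trend test, with the scores fixed in advance;
- keep Fisher's exact test beside it, and say whether it is the overall four-group test or a set of pairwise tests;
- state which of the two tests leads, and that both are exploratory;
- report risk differences of each dose versus placebo with 95% confidence intervals.

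The protocol and the analysis plan should carry the same wording, settled before unblinding. If the analysis plan already contains a trend test, only the protocol text needs aligning.

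The cost is wording and one more test per endpoint, with no extra patients or data. The trend test has less power than Fisher's under a plateau from the low dose, under a downturn or, with equally spaced scores, when only the high dose works. That is the reason to retain Fisher's test.

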○ Patient currently treated for an active malignant disease or prior diagnosis of an active malignant disease who is disease free for less than 1 year. Treatment with anticancer therapy (chemotherapy, immunotherapy, radiotherapy, targeted therapy, or gene therapy) within 3 months before the first administration of the investigational product or at any time during the study	
○ Patient with a history of malignancy within the wound; history of radiation therapy to the wound region	
○ Patients who have undergone wound treatments with growth factors, dermal substitutes, or other biological therapies within the last 30 days or during the study	
○ Patients who received oral or parenteral corticosteroids, immunosuppressants, or cytotoxic agents within 30 days preceding the first study drug administration, or plan to use these medications during the study period	
○ Patients who are pregnant or breastfeeding	
○ Mental condition rendering the patient (or the patient’s legally acceptable representative[s]) unable to understand the nature, scope, and possible consequences of the study	
○ Patients who are incarcerated, including prisoners or patients compulsorily detained for treatment of either a psychiatric or physical (e.g., infectious disease) illness	
○ Therapy with another investigational agent within 30 days of screening, or during the study	
○ Patients who are considered by the investigator to have a significant disease, which can impact the study; patients who are considered not suitable for the study by the investigator	
○ Employee at the study site, spouse/partner or relative of any study staff (e.g., investigator, sub-investigators, or study nurse), or relationship to the sponsor	
Prohibited medication	
○ Oral or parenteral corticosteroids of > 20 mg/week within the past 4 weeks before the screening and during the course of the study (intranasal or inhaled steroids for allergies/asthma or COPD are allowed)	
○ Immunosuppressive or cytotoxic agents within 30 days preceding the first study drug administration and during the study period	
○ Wound treatments with growth factors, dermal substitutes, or other topical biological therapies within the last 30 days of screening and during the study duration

**Table 3 Tab3:** Visit and treatment schedule

Periods	Enrollment/screening	Allocation	Active treatment	Follow-up/close-out			
Visits	Visit 1	Visit 2	Visit 3 to visit 13	14 (EOT)	15	16	17

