For the primary endpoint, the last observation carried forward (LOCF) procedure will be applied. If the visit 14 measurement of wound size is missing, the last available post-baseline measurement will be used.

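### Carry-forward, the analysis-set condition and the closure definition leave amputation, surgical closure, prohibited wound therapy and death without a stated efficacy score, which can bias dose comparisons if such events differ by arm

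*Protocol article*

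**What the plan says.** Four statements in the protocol article bear on this.

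- **Missing data (Statistical analysis).** Last observation carried forward is prescribed for the primary endpoint: "If the visit 14 measurement of wound size is missing, the last available post-baseline measurement will be used". No reason for missingness is excepted.
- **Analysis set (Statistical analysis).** Primary and secondary efficacy are both analysed in the full analysis set: patients with a baseline wound size "who received at least one dose of IMP and have data available at the end of treatment visit".
- **Closure (Study endpoints).** Complete closure during the 12 weeks means "100% re-epithelialization of the wound surface with the absence of drainage". How closure was reached is not mentioned.
- **Prohibited therapy (Table 2).** The prohibited list includes "Wound treatments with growth factors, dermal substitutes, or other topical biological therapies within the last 30 days of screening and during the study duration". Under Protocol deviation, whether a deviation removes a patient from the data set is decided individually before database lock, guided by a Protocol Deviation Plan.

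The article defers analysis details to a statistical analysis plan that is not shown. Amputation or surgical closure of the index ulcer does not appear as an analysis event.

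**The concern.** The Background names amputation and death as the main consequences of delayed healing. These outcomes ought to count against a dose, or at least not help it. Under the rules stated:

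- an ulcer removed or surgically closed before visit 14 has no valid measurement there, so its last pre-event area is carried forward;
- a patient without end-of-treatment data, for example after death, falls outside the set used for every efficacy endpoint, including the >50% response and closure;
- a wound closed with a graft, by surgery or under a prohibited topical product meets the closure definition.

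The trial is meant to find the minimum effective dose, and the Discussion uses the secondary endpoints to plan a phase III trial whose primary endpoint must be complete closure. If such events depend on dose, the wound-area, response and closure results would reflect the scoring convention as well as the drug.

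**Working it through.** **1. The rules side by side.** Carry-forward exists to fill missing visit 14 areas. The analysis set requires end-of-treatment data. If that means a wound area, the set removes the very patients carry-forward is meant to fill. If it means any data, carry-forward reaches only patients who attended without a wound measurement. An ulcer that no longer exists is one such case; a failed image is another. Neither reading gives these events a score of their own.

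**2. Planning inputs (Sample size calculation and power).** Mean reductions are 0.40, 0.45, 0.50 and 0.55, the SD is 0.156 and alpha is 0.05 two-sided. The variance of the means is 0.0125/4 = 0.003125 (stated as 0.003). A four-group ANOVA with noncentral F then has 81.5% power at 23 per group and 79.5% at 22, so the stated 23 reproduces. It does not test this point, but it fixes the effect sizes used below.

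**3. What carry-forward credits.** Assume log-linear healing at the arm's planned rate m. The credit at day d is 1 − (1 − m)^(d/28).

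| m | d = 14 | d = 21 |
|---|---|---|
| 0.40 (placebo) | 22.5% | 31.8% |
| 0.55 (high dose) | 32.9% | 45.1% |

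These are illustrative. A wound heading for amputation may heal more slowly or enlarge, and carry-forward would then carry that.

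**4. Shift of one arm's mean.** Replacing a carried reduction c by 0% in a fraction p of an arm lowers its mean by p × c. With p from 2% to 15% and c from 10% to 40% (all assumed), the shift runs from 0.02 × 10 = 0.2 points to 0.15 × 40 = 6.0 points. The planned step between doses is 5 points.

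**5. High dose minus placebo, assuming c = 20%.**

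- 10% events on high dose, none on placebo. Dropped: 55 − 40 = 15.0 points. Carried: (0.9 × 55 + 0.1 × 20) − 40 = 11.5. Scored 0%: 0.9 × 55 − 40 = 9.5.
- 10% on placebo, none on high dose. Dropped: 15.0. Carried: 55 − (0.9 × 40 + 0.1 × 20) = 17.0. Scored 0%: 55 − 0.9 × 40 = 19.0.
- 5% in both. Carried: (0.95 × 55 + 1) − (0.95 × 40 + 1) = 14.25. Scored 0%: 0.95 × 55 − 0.95 × 40 = 14.25.

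**6. Binary endpoints.** Take a nominal arm of 132/4 = 33. Reclassifying one assisted closure moves the closure rate by 1/33 = 3.0 points. Dropping one non-responder from 16 responders in 33 changes 48.5% to 16/32 = 50.0%, or 1.5 points.

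**7. Cost of a flat 0% score.** Suppose 5% of every arm has an event scored v. The arm mean is 0.95m + 0.05v, and the within-arm variance is 0.95(0.156² + m²) + 0.05v² minus the squared arm mean. Averaged over arms, the SD is 0.184 for v = 0 and 0.164 for v = 0.20. Power at 23 per group is 61% and 72% respectively, and 79% if these patients are dropped.

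**The case against.** A reader might infer that these events can never count as failures. The documents do not support that.

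- The article gives no such rule. It defers details to an analysis plan and a Protocol Deviation Plan, neither of which is shown.
- Prohibited therapy does not by itself trigger carry-forward: the wound can still be measured at visit 14, and the observed area then counts unless the data review excludes the patient.
- Carry-forward is stated only for the primary endpoint. Even if extended to the >50% endpoint, the illustrative credits of 22.5% to 45.1% are all below 50%, so those patients would already be non-responders.
- A patient in the set with no recorded re-epithelialization already counts as not closed, and an amputated site hardly fits a definition that refers to the wound surface.
- Carry-forward can carry an enlarged wound. A flat 0% would then improve the score.
- Eligibility is restricted to non-infected, adequately perfused ulcers, and treatment lasts four weeks, so events may be few. Early terminators should have at least an end-of-treatment examination. Imaging problems could equally explain a missing area.
- Related local adverse events and serious adverse events are counted as a separate endpoint.

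All of this stands, and it narrows the point. It does not remove it. The article chose to state the missing-data rule, the analysis set and the closure definition. An analysis plan that scored these events as failures would have to override the stated carry-forward rule and analysis set, and add a condition to the closure definition.

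**Conclusion.** The point holds in a limited form. Three stated rules, followed literally, allow a patient with amputation, surgical loss of the ulcer or death to enter with a pre-event area or to be dropped, and allow assisted closure to count as healing. The analysis-set condition and the carry-forward rule also need reconciling with each other.

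It would be tempting to conclude that a harmful dose could not look worse on wound area. That is not so: in the example with 10% events on high dose only, carry-forward already lowers the difference from 15.0 to 11.5 points. What the rules leave open is a spread of 5.5 points (15.0 − 9.5) for the same patients, depending on how they are handled. With equal event rates, carry-forward and failure scoring give the same arm difference, so bias requires imbalance, and its direction follows the arm with more events. Event rates and carried reductions are assumptions; the documents give neither. This should be corrected before unblinding, but it does not undermine the design.

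**What to change.** 1. In Statistical analysis, remove the end-of-treatment-data condition from the full analysis set, so that these patients stay in it and the set agrees with carry-forward. State how a patient with no post-baseline area is scored.
2. In Study endpoints, state that index-site amputation, surgical closure or grafting, a prohibited topical therapy on the index ulcer, or death before the assessment counts as non-response on the >50% endpoint and as non-closure.
3. For the continuous primary endpoint, keep carry-forward and add a prespecified sensitivity analysis that ranks these patients worst, or scores them at the worse of 0% and the last observed change. The Kruskal-Wallis test already named in the plan can be used on such ranks. A flat 0% in the primary analysis is not recommended, given the power cost shown and the chance of flattering an enlarging wound.

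The cost is wording. Table 3 already schedules adverse events and concomitant medication through follow-up. Response and closure rates would be slightly lower (3.0 points per reclassified patient in a nominal arm of 33), and the sensitivity analysis would carry some added variance.
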